### Randomization

Randomization between the two groups will be stratified in the individual recruitment centers, based on participants' level of cognitive disorder (two levels: minor or major). Randomization by block permutation will be carried out in order to balance the two groups (experimental and control groups), and to allow the workshops to start in the experimental group, which requires a minimum of four dyads. The block permutations will differ in size to ensure the unpredictability of the random allocation.

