### Participant timeline

There will be three assessments: a baseline assessment (Time 1), another 2 months after baseline (Time 2) and a third 6 months after baseline (Time 3), as shown in Figure 2. Participants will be randomized between two sequences (i) Baseline (Time 1)>Intervention>Time 2>Time 3 or (ii) Baseline (Time 1) >Control>Time 2>Time 3 (as shown in Figure 2). The intervention will be based on seven collective workshops, spread over three half-days (once a week for three consecutive weeks). For participants recruited by Lyon Hospital, the evaluation will also include a driving simulator test at Baseline (Time 1), Time 2 and Time 3.

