### Sample size and data analyses

The self-regulation strategy in driving will be considered beneficial if the score of “Self-Regulatory Practice” increases on average by two points (24) 2 months from inclusion. The number of subjects was computed by considering a Student *t*-test for equal variances between the two groups, with a two-sided alpha risk of 5% and a power of 80%. Based on the sample size calculation, 90 participants per group is considered sufficient to detect differences between the two assessments. Because a 10% loss of dyads is expected during the follow-up period, 100 participants per group will have to be recruited, i.e. a total of 200 participants.

Kolmogorov-Smirnov tests will be used to determine the normality of variables. For demographic, clinical, neuropsychological variables, and scores obtained from scales (e.g., the DPPQ), between-group differences will be examined using Fisher's Exact tests, independent Student *t*-tests or Wilcoxon rank-sum tests, as appropriate. The effect size in the intervention group compared to the control group will be quantified by estimating the difference in mean scores between the 2 groups (experimental vs. control) with a 95% confidence interval. A multiple linear regression model will be performed with DPPQ “Current Self-Regulatory Practices” as the dependent variable, and the level of cognitive impairment at inclusion and other characteristics that may have an effect on the outcome criterion as factors. A mixed-effect linear regression model will also be computed with DHQ, GDS-15, Qol-AD and ZBI as dependents variables, and the group (experimental vs. control) and follow-up time (inclusion, 2 and 6 months) as independent variables. The interaction between the intervention group and the follow-up time will be observed.

The concordance between the performance on the driving simulator and the perception of driving ability measured immediately after simulated driving will be estimated by the Lin concordance correlation coefficient and by the Bland & Altman method for continuous criteria, and by the Cohen Kappa coefficient for ordinal criteria. The number of participants who significantly change their estimation at 2 and 6 months compared to before the intervention will be measured from objective and subjective measures at the different points in time.

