### Procedure

Participants who are more likely to participate in the study will be identified during attendance at the memory clinics or in the geriatric departments of the four centers. The inclusion criteria will be checked during the pre-inclusion visit. During the visit to determine inclusion, a physician will take the medical history and note any comorbidities (including a diagnosis of cognitive disorder). He/she will also perform a sensory-motor examination using the Short Physical Performance Battery (balance, walking speed, chair raising), the Stop Walking when Talking (motor and verbal double task) and the Handgrip strength to detect physical frailty (Fried's criteria). Socio-demographic data and current medication will also be noted. A nurse will perform a visual examination by assessing the uni and binocular distance visual acuity (Monoyer scale) and near visual acuity (Parinaud scale). He/she will also perform a screening for age-related macular degeneration (Amsler grid), explore the visual field (with a finger) and examine the color perception. A neurocognitive examination will be performed by a neuropsychologist using the Victoria Stroop Test, the Trail Making Test (A and B), verbal fluencies (“P” and “Animals” in 2 min), the Rey Figure copy, and Digit Span and Coding from the WAIS-IV.

On the day of the inclusion visit, the neuropsychologist will administer the DPPQ, DHQ, QoL-AD, GDS-15 scales to the participant. Natural caregivers will respond by themselves to the DPPQ and DHQ scales (based on observations made about the participant's behavior), and to QoL-AD, GDS-15, ZBI. The dyads included in the control group will receive the usual medical recommendations on the same day. The dyads included in the intervention group will be invited to the three half-day workshops. Workshops will start as soon as the experimental group contains four dyads. At 2 and 6 months, the neuropsychologist will administer the DPPQ, DHQ, QoL-AD, GDS-15 scales to the participant. Caregivers will complete the DPPQ and DHQ scales, (based on observations regarding the participant's behavior), and the QoL-AD, GDS-15, ZBI on their own. A questionnaire about life events that took place between each visit will also be administered to the patient and the caregiver at 2 and 6 months. For 40 participants recruited in the Lyon center, observations on a driving simulator will be collected at inclusion, at the 2-month visit and at the 6-month visit.

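### The mixed models for DHQ, GDS-15, QoL-AD and ZBI estimate the arm effect as a difference in change from inclusion, which is unbiased but less precise than adjusting for the inclusion score

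*Protocol article*

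**What the plan says.** The protocol article, section Sample size and data analyses, describes the secondary analysis in three steps. It names the outcomes: "A mixed-effect linear regression model will also be computed with DHQ, GDS-15, Qol-AD and ZBI as dependents variables". It gives the fixed effects: "the group (experimental vs. control) and follow-up time (inclusion, 2 and 6 months) as independent variables". It then says which term will be examined: "The interaction between the intervention group and the follow-up time will be observed". It mentions neither the inclusion score as a covariate nor any constraint that the arms share a mean at inclusion.

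Other sections bear on this:

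- Randomization: allocation is by permuted blocks of varying size, intended to balance the two arms.
- Participant timeline: the first assessment comes before the intervention. "Participants will be randomized between two sequences (i) Baseline (Time 1)>Intervention>Time 2>Time 3".
- Procedure: the participant's scales are collected at the start. "On the day of the inclusion visit, the neuropsychologist will administer the DPPQ, DHQ, QoL-AD, GDS-15 scales to the participant". The caregiver completes their own scales, including the ZBI, at the same stage.

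**The concern.** With group, a three-level time factor that includes inclusion, and their interaction, each arm has its own mean at inclusion. The interaction term at a follow-up visit is then the change from inclusion in one arm minus the change in the other. In a randomised comparison with a pre-intervention baseline, subtracting the whole baseline score usually over-corrects. It carries the full sampling noise of the baseline into the contrast, whereas regression adjustment subtracts only the part that predicts follow-up.

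These models serve the secondary objectives on mood, quality of life, caregiver burden and driving habits. Wider intervals than the data allow make a real difference easier to miss. They also make the article's expectation that mood and quality of life will be maintained harder to support. The inclusion scores are already being collected, so the lost precision could be recovered at no cost to participants.

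**Working it through.** **Inputs from the article.** Two-sided alpha 5%, power 80%, 90 analysable per arm, 10% loss, 100 recruited per arm (Sample size and data analyses). No SD is given for any scale, and no correlation between visits.

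**The plan's own figure.** The 90 per arm is for the primary outcome and a 2-point difference. Without an SD it cannot be verified directly. Solving backwards, 90 per arm corresponds to an SD of about 4.79 (normal approximation) or 4.76 (t-test), a standardised effect of 2/4.76 = 0.42. The dropout step reproduces: 90/0.9 = 100.

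**Assumptions.** Outcome SD of 1 at every visit, the same correlation rho between any two visits, n = 90 per arm, complete data. Rho is varied because the document does not give it.

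**Formulas for the arm effect at one follow-up visit.**

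- Planned (difference in change): Var = (2/n) × 2(1 − rho)
- Adjusted for the inclusion score: Var = (2/n) × (1 − rho²)
- Follow-up scores alone: Var = 2/n
- Planned relative to adjusted: 2(1 − rho)/(1 − rho²) = 2/(1 + rho)

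**Example, rho = 0.5.** Planned: (2/90) × 1.0 = 0.0222, SE 0.149. Adjusted: (2/90) × 0.75 = 0.0167, SE 0.129. Follow-up alone: 2/90 = 0.0222, SE 0.149. The 95% CI half-width is 1.96 × 0.149 = 0.29 SD as planned and 1.96 × 0.129 = 0.25 SD adjusted.

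| Assumed rho | SE planned | SE adjusted | Excess variance, complete data | Excess variance, 100 per arm with 10% seen only at inclusion | Power of planned contrast for an effect the adjusted one detects with 80% |
|---|---|---|---|---|---|
| 0.3 | 0.176 | 0.142 | 54% | 48% | 62% |
| 0.5 | 0.149 | 0.129 | 33% | 30% | 68% |
| 0.7 | 0.115 | 0.106 | 18% | 16% | 73% |
| 0.9 | 0.067 | 0.065 | 5% | 5% | 78% |

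The SEs come from the information matrix of the three-visit model, fitted with a free arm difference at inclusion and then with a common inclusion mean. They match the formulas. A simulation of 200 trials at rho = 0.5 gave a variance ratio (common mean to planned) of 0.72, against 0.75 in theory.

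**Comparison with ignoring baseline.** The planned contrast has a smaller variance than follow-up scores alone only if 2(1 − rho) < 1, that is rho > 0.5. At 0.5 they tie; below it the planned contrast is worse.

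**Power illustration.** Carrying the 0.42 SD effect over to the secondary scales, which is an assumption, power is the normal probability below 0.42/SE − 1.96. At rho 0.3 it is 66% planned and 84% adjusted; at 0.5, 80% and 90%; at 0.7, 95% and 98%.

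**The case against.** The strongest reply is that nothing here is wrong. Group, time and their interaction is a valid and common model, unbiased under randomisation and with correct type I error. That stands: the point concerns efficiency only. It is not, however, a detail left to an analysis plan that is not shown. The article itself states the fixed effects and the term to be examined.

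Second, the same section also plans between-arm tests on scale scores and a mean difference with a 95% CI. It is loose about which scales and visits these cover. If they include the secondary scales at follow-up, an unadjusted comparison is already planned, and at low rho the benefit of adjustment is smaller: at rho 0.3 the excess variance over the adjusted analysis is 1/(1 − 0.09) − 1 = 10% rather than 54%, and power in the illustration moves from 80% to 84% rather than from 66%. At rho 0.5 the unadjusted comparison is no better than the mixed-model contrast, and at 0.7 it is worse, so it does not remove the loss there.

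Third, the aim of maintaining mood and quality of life is about change, so keeping inclusion in the model seems natural. Change within each arm can still be described. For the comparison between arms, adjustment for the inclusion score gives the same arm coefficient whether the outcome is the score or its change, so that aim does not require the planned contrast.

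Fourth, constraining the arms to a common inclusion mean assumes that the scales were completed before the dyad knew its allocation. The Participant timeline places baseline inside the randomised sequences, and the Procedure section puts the scales and the control recommendations on the same day without stating their order relative to randomisation. This objection stands and limits that form of the fix.

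**Conclusion.** The point holds as a matter of precision in the secondary analyses. The planned contrast has 2/(1+rho) times the variance of the baseline-adjusted one: 33% more at rho 0.5, 18% at 0.7 and only 5% at 0.9. The size rests on an assumed rho, equal SDs across visits and 90 analysable per arm. The power figures also rest on an effect size borrowed from the primary outcome, so they illustrate the loss and do not predict it.

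A reader might infer more than the document supports:

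- That the planned estimates are biased. They are not, given randomisation.
- That a group effect averaged over all three visits, and so diluted by inclusion, would be read as the treatment effect. The article does not say it will use one; it points to the interaction.
- That the primary outcome or the sample size is affected. The DPPQ analysis uses other methods, and the 90 per arm does not depend on these models.
- That equal baseline means can simply be imposed. The document does not state outright that the inclusion scales precede knowledge of allocation.

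**What to change.** In Sample size and data analyses, redefine the secondary mixed models: outcomes are the 2- and 6-month scores; fixed effects are the inclusion score, group, time (2 and 6 months) and group by time. State that the arm difference with its 95% CI will be reported at 2 months and at 6 months.

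Alternatively, if the sponsor confirms that the inclusion scales are completed before allocation is known, keep inclusion as an outcome and hold the two arms to a common mean there, with arm differences only at 2 and 6 months. The two options are near-equivalent and differ slightly when data are missing, as the expected 10% loss implies, so one should be chosen in advance.

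The cost is a change to the analysis text, plus that confirmation for the second option. No additional data, visits or participants are needed.

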For each task, means and standard deviations of speed, lane position, steering angle, reaction times to traffic lights or unexpected events will be measured. In addition to the objective measures obtained from simulator data, subjective measures will be collected from a questionnaire administered to the participant immediately after each simulator task. While the participant will perform the driving task, the experimenter will fill out the same questionnaire about participant's driving ability (i.e., perception of participant's driving ability). The comparison between the scores obtained from the participant and the experimenter will inform on the participant's driving ability self-awareness. Finally, objective as well as subjective measures will inform on the participant's driving ability and his/her self-awareness of this ability, respectively.

- Mood:

Indicators of mood effects on driving modifications will be measured by the Geriatric Depression Scale 15-item version (GDS 15) (39) in both participants and their natural caregivers at 2 and 6 months.

- Quality of life:

Indicators of quality of life following driving changes will be measured by the Quality of Life in Alzheimer's Disease Scale (QoL-AD) (40) in both participants and their natural caregivers at 2 and 6 months.

-Caregiver burden:

Indicators of caregiver burden following driving changes by the participant will be measured 2 and 6 months by the Zarit Burden Inventory (ZBI) (41) for natural caregivers.

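### Lin's coefficient, Bland-Altman limits and kappa are applied to simulator performance against self-rated ability, which share no scale, while the same-questionnaire pair that defines self-awareness has no stated analysis

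*Protocol article*

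**What the plan says.** All references are to the protocol article.

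- **Performance.** Under Secondary outcomes, in the part on driving performance and self-awareness, six simulator tasks are described. The objective data are: "For each task, means and standard deviations of speed, lane position, steering angle, reaction times to traffic lights or unexpected events will be measured".
- **Perception.** The same part adds that "subjective measures will be collected from a questionnaire administered to the participant immediately after each simulator task". The items, range and scoring of this questionnaire are not given.
- **Same-scale comparator.** During the drive, "the experimenter will fill out the same questionnaire about participant's driving ability". The stated purpose is: "The comparison between the scores obtained from the participant and the experimenter will inform on the participant's driving ability self-awareness".
- **Analysis.** Sample size and data analyses fixes the pair to be compared: "The concordance between the performance on the driving simulator and the perception of driving ability measured immediately after simulated driving will be estimated by". Three methods are named: Lin's coefficient and Bland-Altman where the criteria are continuous, and Cohen's kappa where they are ordinal. The experimenter's score is not mentioned there. The paragraph then plans a count of participants whose estimation changes at 2 and 6 months, drawing on both objective and subjective measures.
- **Objective.** Under Aims and hypotheses, secondary objective (a) is the effect of the programme on self-awareness of driving ability.
- **Other self-awareness indicator.** Under Secondary outcomes and in Table 2, the second part of the Driving Habits Questionnaire (DHQ) is also a self-awareness indicator. The DHQ enters a mixed model with group, time and their interaction.

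**The concern.** Lin's coefficient and Bland-Altman limits assess whether two readings of the same quantity, on the same scale, agree. Lin's coefficient penalises any difference in mean or variance between the two readings, and Bland-Altman subtracts one reading from the other. A speed in km/h minus a questionnaire score is not a quantity. Kappa similarly needs both ratings to fall in the same categories, and no shared categories are described for simulator measures and questionnaire answers.

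If the analysis is run as written, the simulator results would tend to show poor concordance because of units and scales, and could be misread as poor self-awareness. The comparison that the protocol itself says carries the self-awareness information would have no stated analysis.

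**Working it through.** The plan states no figure for this analysis, so there is none to reproduce. The check asks what the planned statistics return when awareness is perfect.

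**Inputs.** The document gives no means or SDs for these measures, so all are assumed. Rating: mean 7, SD 1.5 on a 0 to 10 scale. Simulator measures: as in the table. Perfect awareness is taken as a perfect linear association, r = 1. Where a higher value means worse driving, the sign of Lin's coefficient reverses and its size is unchanged.

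**Formulas.** With means m1, m2 and SDs s1, s2:

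- Lin's coefficient = 2·r·s1·s2 / (s1² + s2² + (m1 − m2)²)
- Bland-Altman limits = (m1 − m2) ± 1.96·√(s1² + s2² − 2·r·s1·s2)

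**Worked case, speed in km/h (mean 78, SD 5).** Lin: 2 × 5 × 1.5 / (25 + 2.25 + 71²) = 15 / 5068.25 = 0.003. Limits: 71 ± 1.96 × 3.5 = 64.1 to 77.9.

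| Simulator measure (assumed mean, SD) | Lin's coefficient, size at r = 1 |
|---|---|
| Speed, km/h (78, 5) | 0.003 |
| The same speed in m/s (21.67, 1.39) | 0.019 |
| Reaction time, s (1.2, 0.3) | 0.025 |
| The same reaction time in ms (1200, 300) | 0.0006 |
| SD of lane position, m (0.30, 0.08) | 0.005 |
| The same in cm (30, 8) | 0.040 |

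For the same speed data, the Bland-Altman limits move from 64.1 to 77.9 (km/h) to 14.5 to 14.9 (m/s).

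**Sensitivity to the rating mean.** With a rating mean of 6, reaction time in seconds gives 0.9 / (0.09 + 2.25 + 4.8²) = 0.9 / 25.38 = 0.035. Speed of 80 km/h (SD 5) gives 15 / (25 + 2.25 + 74²) = 15 / 5503.25 = 0.003. Both lie within the range in the table.

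**Would standardising rescue it?** If both measures were converted to mean 0 and SD 1, Lin's coefficient becomes 2r / 2 = r, the ordinary correlation. The mean difference is then zero by construction, so systematic over-rating could not appear.

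**Same formulas on the same-questionnaire pair.** Participant and experimenter, SD 1.5 each (assumed):

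- Perfect agreement: Lin 1.00, limits 0 to 0.
- r = 0.5, no bias: Lin = 2.25 / 4.5 = 0.50, limits ±1.96 × 1.5 = −2.94 to 2.94.
- r = 0.5, participant over-rates by 1.5 points: Lin = 2.25 / (4.5 + 2.25) = 0.33, limits −1.44 to 4.44.

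Here the statistics separate agreement from over-rating and are in the units of the questionnaire.

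**The case against.** The best defence is that performance, in the analysis section, means the experimenter's rating. Kappa is planned for ordinal criteria, yet the objective measures listed are continuous. The only described pair that could share ordinal categories is participant and experimenter on one questionnaire. On that reading the methods are valid and the sentence is merely loose. The reading is possible but not the natural one. The protocol calls the experimenter's score a perception, says performance is evaluated by the driving tasks, and lists objective simulator measures beside the questionnaire in Table 2. The analysis paragraph itself ends by referring to objective and subjective measures. Even on this defence the sentence needs rewording.

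It is also fair that the size rests on assumed scales, and that graded performance scores might be planned in a document not shown. The values near zero are illustrations; the dependence on units is not an assumption.

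Two stronger readings are tempting, and the document supports neither:

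- **A reader might infer that self-awareness is never compared between arms.** The second part of the DHQ is a self-awareness indicator, and the DHQ has a group-by-time mixed model, although that model does not single out the second part. What is not stated is an arm comparison of the simulator-based measure, and an unseen analysis plan may hold it.
- **A reader might infer that kappa will be unweighted.** The article does not say so, and the choice of weights is commonly left to the analysis plan.

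**Conclusion.** The point holds as a mismatch between two sections and as a badly chosen pair of measures. As naturally read, the analysis section applies agreement statistics to quantities with no common scale. Lin's coefficient is then about 0.0006 to 0.04 in size under perfect linear association, on the assumed scales, and it changes with the unit alone. The pair that the protocol says informs self-awareness has no stated analysis.

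The reach is limited: one secondary measure in 40 Lyon participants out of 200. The primary outcome and the DHQ-based assessment of self-awareness are unaffected. It should be corrected before analysis, because no later detail can make agreement statistics meaningful between a physical measurement and a questionnaire score.

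**What to change.** In Sample size and data analyses:

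1. Apply Lin's coefficient, Bland-Altman limits and kappa to participant versus experimenter scores on the same questionnaire, in line with Secondary outcomes.
2. Relate the objective simulator measures to the participant's self-rating by rank correlation or regression, which need no common scale.
3. Because objective (a) is an effect of the programme, the participant-minus-experimenter difference can also be compared between arms at 2 and 6 months, adjusted for its baseline value and labelled exploratory. With an assumed 20 per arm, no loss to follow-up and no adjustment, the 95% confidence interval for a difference in means has a half-width of about 2.02 × √(2/20) = 0.64 SD.

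The cost is wording only. The participant questionnaire, the experimenter questionnaire and the simulator measures are all already planned.

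### Agreement statistics are assigned to simulator measures versus a questionnaire rating, which have no stated common scale, so the result depends on the units; the participant–experimenter pair that suits them is not named

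*Protocol article*

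**What the plan says.** The last paragraph of Sample size and data analyses in the protocol article names the pair to be compared: "The concordance between the performance on the driving simulator and the perception of driving ability measured immediately after simulated driving will be estimated by" three statistics. Two of them serve the continuous measures: "estimated by the Lin concordance correlation coefficient and by the Bland & Altman method for continuous criteria". Ordinal measures are handled separately: "by the Cohen Kappa coefficient for ordinal criteria".

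Secondary outcomes, under driving performance and self-awareness, describes the two sides of that pair. On the performance side, "For each task, means and standard deviations of speed, lane position, steering angle, reaction times to traffic lights or unexpected events will be measured". On the perception side, "subjective measures will be collected from a questionnaire administered to the participant immediately after each simulator task". The questionnaire's range and response format are not given, and no conversion of simulator output to its scale is stated.

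The same section adds a third quantity: the experimenter completes the identical questionnaire about the participant while the task is being driven. It then says: "The comparison between the scores obtained from the participant and the experimenter will inform on" self-awareness in the participant. The analysis section does not mention that comparison.

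**The concern.** Lin's coefficient measures how far paired values lie from the line of identity, and Bland-Altman analysis works on the difference between the two values. Both presuppose that equal numbers mean equal things. Kappa has the same requirement for categories: both sides must use the same set. Speed, lateral position, steering angle or reaction time on one side and questionnaire points on the other do not meet it.

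The article therefore has a mismatch between two sections. The outcomes section has a pair on one scale and says it informs on self-awareness. The analysis section gives the agreement statistics to a different pair. Self-awareness of driving ability is secondary objective (a) in Aims and hypotheses. If the analysis were run as worded, the simulator contribution to that objective would be a set of coefficients and limits that change with the unit of recording, and so could not show whether the programme altered awareness.

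**Working it through.** **Inputs.** The pair and the statistics come from Sample size and data analyses; the nature of the measures comes from Secondary outcomes. The article gives no means, SDs or questionnaire range, and no figure of its own to reproduce. All values below are assumptions chosen to show the range.

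**Formulas.**
- Lin's coefficient: CCC = 2·r·s1·s2 / (s1² + s2² + (m1 − m2)²)
- Bland-Altman: bias = m1 − m2; limits = bias ± 1.96·SD of the difference. At r = 1 that SD is |s1 − s2|.

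Set |r| = 1, so that across drivers the self-rating tracks performance perfectly. The assumed rating is mean 6, SD 2 on 0–10; mean 3.5, SD 1 on 1–5; or mean 60, SD 20 on 0–100.

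| Simulator measure (assumed mean, SD) | 0–10 | 1–5 | 0–100 |
|---|---|---|---|
| Mean speed, km/h (75, 8) | 0.007 | 0.003 | 0.46 |
| SD of speed, km/h (5, 2) | 0.89 | 0.55 | 0.02 |
| SD of lane position, m (0.30, 0.10) | 0.011 | 0.018 | 0.001 |
| SD of steering angle, degrees (6, 2) | 1.00 | 0.36 | 0.02 |
| Reaction time, s (1.2, 0.3) | 0.044 | 0.094 | 0.003 |
| Reaction time, ms (1200, 300) | 0.0008 | 0.0004 | 0.009 |

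Entries are the absolute value of CCC.

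**Same data, different unit.**
- Reaction time against 0–10, in seconds: 1.2 / (0.09 + 4 + 23.04) = 1.2 / 27.13 = 0.044. In milliseconds: 1200 / (90000 + 4 + 1425636) = 0.0008.
- Mean speed against 0–10: 32 / (64 + 4 + 4761) = 0.007. Multiply every rating by 10: 320 / (64 + 400 + 225) = 0.46.
- SD of steering angle against 0–10: 8 / (4 + 4 + 0) = 1.00, only because the assumed means and SDs coincide.

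Nobody's awareness differs between the two versions of a pair.

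**Sign.** If a higher rating means better driving and a higher reaction time or variability means worse driving, perfect awareness is r = −1 and each of those entries becomes negative. The steering example would read −1.00. A simulation of 40 drivers, with reaction time in seconds against a 0–10 rating and perfect awareness, gave a mean CCC of −0.043 (95% range −0.065 to −0.026).

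**Bland-Altman.** Mean speed against 0–10: bias = 75 − 6 = 69; limits = 69 ± 1.96 × 6 = 57.24 to 80.76. These are kilometres per hour minus points and have no interpretation.

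**The pair on one scale.** Participant and experimenter on the same form (mean 6, SD 2 each) give CCC = 8 / 8 = 1.00 when they agree perfectly, and 8 / (4 + 4 + 1) = 0.89 when the participant ranks perfectly but over-rates by one point. Here the coefficient responds to over-rating, as a measure of self-awareness should.

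**Standardising both sides.** With z-scores aligned in direction, means are equal and SDs are 1, so CCC = 2r / 2 = r. It then carries association only, and Bland-Altman bias is zero by construction.

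**The case against.** The strongest reply is that performance in the analysis paragraph means the experimenter's rating. Kappa is planned for ordinal criteria, yet the simulator measures listed are all continuous, so some rated or scored version of performance may have been in mind. All three statistics would suit the participant–experimenter pair. This reading is possible. It sits poorly with the close of the outcomes section, which assigns objective measures to ability and subjective measures to self-awareness, and with the next sentence of the analysis paragraph, which again separates the two. If it is what was meant, the analysis paragraph needs the same edit.

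A second reply is that a condensed article leaves item definitions and derived scores to the full protocol or analysis plan. That stands in part: a full plan could define a simulator score on the questionnaire's scale. But the article does not merely omit detail. It states a pair and a statistic that do not fit each other, and nothing in it points to such a score.

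A reader might also infer more than the text supports:
- That agreement must come out near zero. It does for many of the assumed pairs, but not in general: the table has 0.46, 0.89 and 1.00. A falsely high value is as misleading as a low one.
- That the result would be taken as lack of self-awareness in both arms. That is speculation, and a plot of unlike units might well be noticed.
- That self-awareness rests on this analysis alone. The second part of the DHQ also measures it, the DHQ enters the mixed model, and caregivers report on the participant's driving.

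**Conclusion.** The point holds as a misfit between the stated pair and the stated statistics. Read as written, Lin's coefficient and the Bland-Altman limits depend on arbitrary units and cannot be interpreted as self-awareness; kappa is likewise undefined without shared categories. The numerical range, below 0.001 to 1.00 in size with either sign, rests on assumed means, SDs and rating scales. The conclusion that the units drive the result follows from the formulas and does not depend on those values. It would fall away only if a document not shown defines performance on the questionnaire's scale.

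The reach is limited: one secondary analysis in the simulator subsample of 40 Lyon participants out of 200. The primary DPPQ comparison is untouched, as is the DHQ-based measure of self-awareness.

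**What to change.** In the last paragraph of Sample size and data analyses:

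1. Name the participant's and the experimenter's scores on the same questionnaire as the pair for Lin's coefficient and Bland-Altman limits (continuous scores) and for kappa (ordinal items).
2. Relate the participant's self-rating to the objective simulator measures by a method that needs no common unit: Spearman correlation, or regression of the self-rating on task performance. State the direction of each measure so that signs are aligned.
3. If a simulator score on the questionnaire's scale is intended instead, define it before the data are examined.

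The cost is wording only. The simulator data and both completed questionnaires are already in the planned data collection.
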